### Study objectives

The F0 of singing and its impact on neonatal brain development remains under-explored, particularly in the context of NICU environments. Current literature lacks detailed insights into how F0 variations, influenced by the biological sex and kinship of the singing source, affect the short-term neurophysiological responses of premature infants. Therefore, this exploratory study is developed as a complementary ‘single-arm’ extension of the randomized controlled trial (RCT; clinicaltrials.gov unique identifier: NCT06398912), aiming to address this research gap by isolating and further examining the neurophysiological mechanisms identified in the original RCT protocol. Specifically, this single-arm study focuses exclusively on the intervention group structure to investigate how different F0 profiles from human voices across various kinship dynamics (i.e., mother, father, male, and female music therapists) influence the brain activity of NICU infants.

The rationale and value for following this presentation approach at this stage (acknowledging of course the inherent limitations of this approach such as the absence of a direct comparison group and weaker causal interpretations) is twofold. First, and most importantly, reporting the single-arm protocol design and its preliminary data alone contributes significantly to the broader field by offering a rigorous methodological template, which can guide future research and intervention designs in similarly sensitive neonatal settings. Second, it allows for a detailed examination of individual and within-subject EEG response patterns to take place, providing nuanced insights that might be obscured by group-level analysis typical in RCTs. Therefore, we believe the current approach is scientifically justified, as it forms a critical foundation for subsequent comprehensive analyses within the context of our broader RCT.

Based on the above, the primary research question of the study reported here is: *Does a structured sound and music-based intervention, delivered by four different facilitators (mother, father, male and female music therapist) as determined by their fundamental frequency (F0) and kinship, result in a differentiated short-term electroencephalographic effect footprint in NICU infants?*

Our research hypotheses are as follows:

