**Fig 2 pone.0328211.g002:**
[figure not shown]
Study Protocol Flow Chart.

In this design, although the EEG will be the primary tool of data collection and analysis, the rationale for incorporating video data is multifaceted. Firstly, the video recordings will complement the electroencephalogram (EEG) recordings in offering a comprehensive parallel view of the infants’ neural and behavioral responses. Furthermore, the videos will serve as a tool for quality control by ensuring that the prescribed research protocol is uniformly followed by all facilitators, contributing to the scientific integrity of the research. Finally, the videos will allow for a later examination of any synchrony or coordinated interactions between the infant and the facilitator, shedding light on phenotypical – not able to be measured by the EEG – aspects of the intervention.

The live singing intervention will be delivered by four different profiles of individuals-facilitators: a male music therapist, a female music therapist, the mother, and the father of the newborn. During the delivery of the intervention (explained in more detail below), there will be five ‘conditions’ measured: Silence1 (180 seconds), Note A (60 seconds), Silence2 (180 seconds), Song (90 seconds) and Silence3 (180 seconds).

It is important to note that the study protocol will be conducted in a dedicated room, largely isolated from the ambient noise typically found in the rest of the NICU. This aspect of the study design is crucial for two main reasons:

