Firstly, it will ensure the comfort and safety of the participating newborns. All actions taken in the context of the NICU require adherence to the recommended standards for the NICU sound environment. Therefore, the importance of a well-managed acoustic environment in reducing stress and discomfort for our participating infants is of paramount importance. Such a consideration has been consistently highlighted both for clinical and research settings alike [32] and a sound-controlled room within the NICU seems to be the only viable option for achieving the necessary level of sound management for our participants, without disrupting other clinical operations. More specifically, in the NICU context, when considering the operational sound as outlined by White, Smith, Shepley, et al. [31], the combination of continuous background sound and operational sound should not exceed an hourly L_eq_ of 45 dB and an hourly L_10_ of 50 dB, both A-weighted slow response, with transient sounds or L_max_ not exceeding 65 dB. Our study, with sound exposure lasting less than 3 minutes per hour, will strictly adhere to these guidelines. However, the transient nature of singing, distinct from the continuous and better-controlled sound pressure levels typically found in continuous speech, might lead to brief instances where we slightly exceed these thresholds by about 15 dB. According to evidence, even professional singers, and more so untrained individuals like the parents participating in our study, are not able to produce transient peak Sound Pressure Levels (SPLs) below 78–79 dB when singing softly [70]. However, it has been noted that in environments with lower ambient noise, humans can more easily maintain a soft vocal output because the reduced background sound allows for greater control and minimizes the need to compensate with higher volume [71]. Therefore, we believe that a dedicated room will significantly aid in ensuring the correct application and viability of the aforementioned recommendations – by providing an acoustically controlled setting that minimizes ambient noise and facilitates softer singing performance – as compared to the open NICU floor, thus preventing the intervention from inadvertently exceeding the recommended soundscape limits.

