Finally, to ensure the best possible implementation of the intervention – particularly regarding the singing process – all parents of participants who meet the study’s inclusion criteria will receive 30 minutes of training before the actual intervention. This training will be conducted by a member of the research team who is a professional musician, singer, and music therapist. This pre-intervention session aims to equip parents with the necessary skills and understanding to enhance the intervention’s effectiveness, ensuring close consistency among the different facilitators. Additionally, the training session is designed to provide a calming influence on the parents, which can reduce stress and anxiety for both the infants and their caregivers during the delivery of the intervention. We believe that this pre-intervention training will empower parents as active participants in their child’s care, improving adherence and contributing to a more supportive and therapeutic environment throughout our study in the NICU.

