Furthermore, by employing electroencephalography (EEG) and utilizing a custom-made and adapted EEG (pre)processing pipeline, the effects of our live singing intervention on premature infants can be studied in greater detail. This advanced neuroimaging approach allows for a nuanced understanding of how different auditory stimuli influence brain activity in this vulnerable population. As discussed in previous work [30], neuroimaging-guided interventions should be more extensively introduced in the NICU because they can provide real-time insights into the brain’s response to external stimuli, capturing dynamic changes that might not be observable through behavioral measures alone. In this regard, our protocol not only enhances the precision of our study but also contributes to the development of more tailored applications in the future, optimizing music-based interventions to suit the unique neurodevelopmental needs of each infant in the NICU.

Finally, it is important to point out that the study design we decided to implement includes the chosen variety of caregivers to allow us to provide a more comprehensive insight into the role of emotional and social factors evident and embedded in the treatment process of premature infants in real-world situations and environments. For that matter, on the one hand, the inclusion of both parents in the protocol ensures that the study captures potential sex-specific effects, which could be related to differences in voice register or emotional bonding, while, on the other hand, incorporating professional music therapists as facilitators offers a standardized comparison to the former set of caregivers, helping to differentiate the effects of kinship as well as musical and clinical expertise related to the implementation of music-based interventions in this sensitive context. This diversity in caregivers could not only enrich the study’s findings but may also enhance the generalizability of its results, ultimately leading to more comprehensive recommendations for NICU music-based interventions.

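### Kinship coincides exactly with professional status across the four singers, so the design cannot separate kinship from musical or clinical expertise, as the Discussion says it helps to do

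*Protocol article*

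**What the plan says.** Methods, Study design, fixes the singers as "a male music therapist, a female music therapist, the mother, and the father of the newborn". The research question under Study objectives describes these four profiles "as determined by their fundamental frequency (F0) and kinship", and H1 and H0 both use kinship as an explanatory attribute. H0 also names an interaction between F0 and the kinship profile.

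On expertise, Study design contrasts professionals with lay singers when it discusses how softly people can sing: "even professional singers, and more so untrained individuals like the parents participating in our study". The Intervention section states that parents "will receive 30 minutes of training before the actual intervention", with the aim of "ensuring close consistency among the different facilitators". The Discussion describes the unrelated pair as professionals: "incorporating professional music therapists as facilitators offers a standardized comparison to the former set of caregivers". The same sentence then gives the claimed benefit: "helping to differentiate the effects of kinship as well as musical and clinical expertise".

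Under Outcomes and statistical analysis, the model has condition and facilitator as fixed effects and infant as the random effect. Challenges and limitations covers heterogeneity of the infants, the acoustic environment and the parents' emotional state. It does not mention that kinship and expertise move together.

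**The concern.** To tell two attributes apart, a design needs at least one cell in which they differ. Here every related singer is a parent without professional training and every unrelated singer is a professional. A difference between parents and therapists may come from kinship, from vocal or clinical skill, or from a mixture in which the two partly cancel.

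What is at stake is interpretation. The research question and hypotheses treat kinship as an explanation, the Discussion lists the variety of caregivers in kinship and voice register as a key strength, and it already offers biological kinship as a possible reason for the father's result. The article also presents itself as a template for other groups, who could take over the claim along with the design.

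**Working it through.** **Inputs.** The facilitator list and the parents' status come from Study design, the training from Intervention, the therapists' status from the Discussion, and the model terms from Outcomes and statistical analysis. Sex stands in for F0, as in H1.

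| Facilitator | Kin K | Professional E | Female F |
|---|---|---|---|
| Mother | 1 | 0 | 1 |
| Father | 1 | 0 | 0 |
| Female therapist | 0 | 1 | 1 |
| Male therapist | 0 | 1 | 0 |

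**1. Aliasing.** E = 1 - K in every row, so the correlation of K with E is -1.

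**2. Rank.**
- Intercept, K, F, E: 4 columns, rank 3.
- Intercept, K, F, K×F: 4 columns, rank 4. This already uses up the four facilitator means.
- Adding E to the second set: 5 columns, rank still 4.
- E×F = (1 - K)×F = F - K×F, so adding E×F gains nothing either.

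**3. What each contrast estimates.** Write a facilitator mean as μ + κK + φF + εE + γKF + ηEF.
- Parents minus therapists: D = (κ - ε) + (γ - η)/2. Without interactions, D = κ - ε.
- Interaction, (mother - father) - (female therapist - male therapist): (φ + γ) - (φ + η) = γ - η.
- Mother minus father: φ + γ. No expertise term enters.

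Without interactions, κ = D + ε, so the kinship share is κ/D = 1 + ε/D. For D above zero, the share exceeds 1 when ε is positive and is negative when ε is below -D. The data set no bounds on it.

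**4. Sample size.** The article's own figure reproduces: λ = 0.35² × 14 × 5 × 0.75 / (1 - 0.5) = 12.8625, critical F 2.845 on 3 and 39 df, power 0.827 (stated as 0.83). It does not bear on this point. Repeating the four rows for 14 infants leaves the rank at 4 for 5 columns.

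**5. Where it falls in the preliminary results.** From Table 3, mother minus the two therapists is 707.362 - 131.442 = 575.920 and 707.362 - 297.398 = 409.964 µV², with reported p = 0.002 and 0.025. Mother minus father is 707.362 - 393.818 = 313.544 µV², p = 0.085. The two comparisons below 0.05 are the two that carry the aliasing.

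**The case against.** The disputed words are one hedged sentence in the Discussion. It can be read loosely as saying that parents and therapists differ on a bundle of attributes and that the comparison captures the bundle. Expertise is in no hypothesis, outcome or model term. The research question and H1 already name the facilitators, the results are reported by facilitator, and no pooled related-versus-unrelated test is specified. The study is exploratory and its findings are called preliminary. Delivery is standardised by distance, tuning fork, a common lullaby and a guided tempo, which together with the training may narrow the skill gap.

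Much of this stands, and it limits the repair to the attribution to kinship. It does not rescue the sentence: differentiating effects most naturally means telling them apart. Narrowing the gap does not cross the two attributes, and an exploratory aim does not make an unidentified effect estimable. A parent could happen to be musically trained, but the article describes no recording or use of that.

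A reader might infer more than the documents support:
- *That the parent-therapist differences are really due to expertise, or that kinship explains somewhere between none and all of them.* Neither follows. The two effects can have opposite signs, so the share is simply unidentified.
- *That the Table 3 means measure the problem.* A parent-minus-therapist contrast can be computed from them, but it would be a contrast built after the fact on five infants with very variable values. The argument is structural and does not need it.
- *That calling the parents untrained contradicts training them.* The remark in Study design concerns soft singing by lay people, and the training comes before the intervention. The two are compatible.
- *That H1 fails as a whole.* Its mother-father comparison is untouched.

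**Conclusion.** The point holds as a matter of design. With these four facilitators, kinship and professional status are perfectly aliased. The kinship main effect cannot be separated from expertise, and the F0-by-kinship interaction cannot be separated from an expertise-by-sex interaction, at any sample size. Only an outside assumption would do it, for example that expertise has no effect or, for the interaction, the same effect in both sexes. The article states no such assumption, and its own sentence treats expertise as having an effect of its own.

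The Discussion therefore claims a property that the design lacks, and the limitations section omits it. The conclusion rests on the described roles: parents as lay singers with brief training, therapists as professionals. It affects what may be concluded about kinship. It changes no endpoint, sample size or model.

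**What to change.** 1. Withdraw the Discussion statement that the therapists help to tell kinship and expertise apart.
2. Where Study objectives, the hypotheses and the Discussion (the listed strengths and the comment on the father's voice) attribute facilitator differences to kinship, interpret parent-therapist contrasts as briefly trained parent versus professional music therapist. The naming of the four facilitators can stay.
3. Add to Challenges and limitations that kinship, vocal training and clinical expertise are not separable in this design, that this extends to the F0-by-kinship interaction, and that the mother-father contrast is not affected.

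The cost is wording only, with a less specific conclusion about kinship. Separate estimation would need cells that are not planned. As an illustration, unrelated lay singers of both sexes would give the model with kinship, sex and expertise full rank (4 of 4, variance inflation for kinship 1.33). That is a different study and is not proposed here.

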### Challenges and limitations

Despite the strengths of our study, certain challenges and limitations must also be acknowledged. First, the heterogeneity of the study population, which may potentially include infants with varying degrees of prematurity – as defined by their gestational age – and differing health profiles, may introduce significant variability and complicate the interpretation of the results, as the infants’ responses to the live singing intervention may be influenced by factors beyond the scope of the study. For instance, the inclusion of participants with diverse medical histories, while increasing the generalizability of the findings, also necessitates careful consideration in data analysis and further clinical implementation to account for these differences. Furthermore, external factors, such as the NICU environment, could also influence the study’s conduct and the quality of the data collected. The acoustic environment for once, despite being controlled within the study’s dedicated room, may still introduce variability that could affect the infants’ responses, while the fragile emotional and psychological state of the parents, who are also facilitators in the study, could impact the delivery and reception of the live singing intervention. These factors, although managed to the greatest extent possible, remain potential sources of variability that could influence the outcomes.

Despite these challenges, the potential impact of this study remains highly significant. Its future findings, for once, could be easily integrated into existing neonatal care practices, offering healthcare providers a scientifically grounded method for enhancing the care of premature infants. Furthermore, the broader impact of this study could be substantial as the insights gained from the differential effects of maternal, paternal, and therapist-facilitated singing on neonatal brain activity could inform wider public health strategies aimed at improving neurodevelopmental outcomes for premature infants. Finally, this research may also encourage the expansion of music-based interventions in neonatal care units worldwide, particularly in regions where such practices are not yet widely implemented.

## Conclusion

As this study is still in progress, it is essential to recognize that the findings presented here are preliminary, based on an initial analysis cohort. Therefore, the continuation and completion of the study will be critical for validating these early results and for providing a more comprehensive understanding of the effects of the specific music-based intervention on neonatal brain development. That said, several areas for further investigation have emerged from the process of structuring, fine-tuning, and implementing our study protocol, suggesting for future research to explore the long-term effects of this and other similar interventions, particularly in terms of cognitive and behavioral outcomes as the infants develop. Additionally, more research is needed to understand the specific mechanisms through which other dynamic soundscapes and modes of musical delivery may influence the infants’ brain activity, leading to more targeted and effective interventions. For all the above, it is our hope that the detailed report of our study protocol and its preliminary results provided here, may help future researchers better accommodate their investigation needs and study hypotheses in the emerging field of music-based interventions in the NICU with the help of neuroimaging tools and particularly electroencephalography, leading to new horizons of applicable treatment in this very sensitive yet crucial environment for human development.
